### Randomization

A total of 24 participants will be selected and receive a different treatment based on allocation to group A or B. For participants allocated to group A (n=12), NovaBone Putty and AmnioGuard will be placed into the osseous defect, and for participants allocated to group B (n=12), osseous defects will be treated with NovaBone Putty and then A-PRF membrane. Participants will be randomly allocated into the 2 treatment groups (NovaBone Putty, A-PRF, and AmnioGuard) using a computer-generated randomization sequence. The randomization list was created using an online random number generator, ensuring equal distribution of participants across both groups. Allocation concealment will be maintained by an independent clinician who is not involved in the clinical procedures or outcome assessments. Group assignments will be revealed only after patient enrollment and consent, thereby minimizing selection bias.

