#### Inclusion Criteria

The inclusion criteria are as follows: (1) at least 1 or 2 interproximal infrabony osseous defects that may be seen on radiography, with a PPD of at least 5 mm and clinical attachment loss of at least 5 mm after starting treatment; (2) clinical and radiographic measurements showing that the intraosseous component of the lesion is ≥3 mm deep (intraoperative assessment will confirm this); (3) defect radiographic base of at least 3 mm coronal to the tooth’s apex; and (4) keratinized gingiva surrounding the test teeth of at least 3 mm wide to completely hide the deficiency with soft tissue.

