### Procedure

#### Overview

Participants will be enrolled and randomly assigned to the interventions by the researchers in charge of the therapy application. Outcome evaluations were performed on the study participants in accordance with the described procedures and outcome measures. The 15-mm University of North Carolina (UNC-15) probe, which measures plaque index, bleeding on probing, probing depth, pocket depth, and clinical attachment loss, will be used to evaluate participants’ periodontal clinical characteristics. Every patient will receive lessons on proper brushing technique as well as a demonstration of good oral hygiene practices.

Following a thorough examination and diagnosis, the first course of treatment will involve root planing under local anesthesia, supragingival and subgingival scaling, and recommendations on oral hygiene. If necessary, a coronoplasty will be carried out. Instructions for plaque control will be repeated until the patient’s plaque score is less than 1. Six weeks after the initial therapy is finished, a re-evaluation will be conducted to assess the patients’ reaction to the treatment and confirm the necessity of periodontal surgery.

A specially made occlusal acrylic stent will be used to standardize the probe’s location and angulations. The occlusal stent will be constructed using acrylic on a cast model created from an alginate impression. The occlusal stent covers the occlusal surface of the tooth being treated as well as the occlusal surfaces of at least 1 tooth that is mesially and distally next to the afflicted tooth. The stent will also be expanded to cover the coronal part of the teeth. A reference point (slot) will be made on the stent at the deepest point of the impacted tooth to allow for repeatable periodontal probe placement. The apical border will be linear and serve as a fixed reference point.

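### The arm may be disclosed from enrolment and consent onward, but the last inclusion criterion is settled at surgery, no study defect is fixed beforehand, and two sections disagree on who assigns

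*Protocol article*

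**What the plan says.** Four statements in the protocol article bear on this point.

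- **When the arm is disclosed.** Methods, Randomization: "Group assignments will be revealed only after patient enrollment and consent, thereby minimizing selection bias". No later milestone is named.
- **When eligibility is settled.** The second inclusion criterion reads "clinical and radiographic measurements showing that the intraosseous component of the lesion is ≥3 mm deep (intraoperative assessment will confirm this". The final judgement is therefore made with the flap open.
- **How many defects.** The first inclusion criterion admits patients with "at least 1 or 2 interproximal infrabony osseous defects that may be seen on radiography". The article does not say which defect is the study defect or when it is named.
- **Who assigns.** Randomization states: "Allocation concealment will be maintained by an independent clinician who is not involved in the clinical procedures or outcome assessments". Procedure, Overview states: "Participants will be enrolled and randomly assigned to the interventions by the researchers in charge of the therapy application".

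There is also a check between enrolment and surgery. Six weeks after initial therapy "a re-evaluation will be conducted to assess the patients’ reaction to the treatment and confirm the necessity of periodontal surgery". Its order relative to randomisation is not given.

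**The concern.** Concealment protects a trial only if every decision on who and what enters the analysis is made before the arm is known. Here the stated rule stops at consent, while one eligibility decision remains open until surgery. The article nevertheless presents the rule as enough to limit selection bias.

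If the operator knows the arm when judging the opened defect, a borderline depth can be called differently in the two arms. If allocation comes before the study defect is named, a patient with two eligible defects offers a second choice of the same kind. The Procedure section makes this more plausible, because it places assignment with the people who operate.

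With 12 patients per arm, a few such decisions carry weight, and the sample size calculation shows no allowance for exclusions. An analysis plan could not repair this afterwards, because the timing of disclosure is a matter of trial conduct.

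**Working it through.** **1. Order of events as written**

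| Step | Source | Arm known? |
|---|---|---|
| Enrolment and consent | Randomization | No; disclosure permitted from here on |
| Re-evaluation six weeks after initial therapy | Procedure, Overview | Not stated |
| Choice of study defect | Not stated | Not stated |
| Depth of at least 3 mm confirmed at surgery | Inclusion Criteria | Not excluded by the text |

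Nothing places disclosure after the last row. The occlusal stent fixes the probing point on the treated tooth, but not which tooth or defect is chosen.

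**2. The plan's own sample size.** Inputs from Sample Size Estimations: means 8.6 and 6.9 mm, SDs 1.17 and 1.10 mm, z values 1.96 and 1.64, r = 1.

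n = (1.96 + 1.64)² × (1.17² + 1.10²) / (8.6 − 6.9)² = 12.96 × 2.5789 / 2.89 = 11.56, rounded up to 12. The printed figure reproduces.

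**3. Loss of precision if patients drop out at surgery.** Pooled SD = √(2.5789 / 2) = 1.136 mm; difference 1.7 mm; two-sided t test at 0.05. The noncentrality parameter is 1.7 / (1.136 × √(1/n₁ + 1/n₂)), which is 3.67 at 12 v 12 and 3.35 at 10 v 10.

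| Patients analysed | Power |
|---|---|
| 12 v 12 | 93.9% |
| 10 v 12 | 91.4% |
| 10 v 10 | 88.6% |
| 9 v 9 | 84.6% |

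The exact t test gives slightly less than the planned 95% even with nobody lost, because the plan's formula uses normal quantiles. These figures are for probing depth, a secondary outcome. The article gives no SD for the primary outcome, bone fill on radiographs.

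**4. Selection bias, under assumptions only.** The table in step 3 measures lost numbers, not bias. To show a possible scale of bias, 20,000 trials with no true effect and 12 patients per arm were simulated. The assumptions are a correlation of 0.3 to 0.7 between a defect's prognosis and its outcome, a within-patient correlation of 0.3, and selection in one arm only. The documents give none of these values.

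| Scenario | Bias (SD) | Type I error |
|---|---|---|
| 2 worst-prognosis patients of 12 excluded | 0.08 to 0.19 | 5.3% to 7.8% |
| 3 worst-prognosis patients of 12 excluded | 0.12 to 0.27 | 5.8% to 10.0% |
| Better of two defects taken; half of patients have two | 0.08 to 0.17 | 5.3% to 6.8% |
| Better of two defects taken; all patients have two | 0.14 to 0.33 | 6.1% to 12.3% |

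Without selection the same simulation gave 4.7% to 5.2%, so the low ends are barely above nominal. All four scenarios assume that selection follows prognosis exactly, which makes them unfavourable cases.

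**The case against.** The strongest reply is that the disclosure clause sets an earliest time, not a fixed one. Since the 3 mm depth is itself an inclusion criterion, enrolment might be regarded as complete only once surgery has confirmed it. That reading is possible, but the article does not state it and treats enrolment and consent as sufficient. The objection turns the point into a route left open rather than a bias shown to occur, and the conclusion is limited accordingly.

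Second, depth is screened clinically and radiographically before surgery, so few defects may fail. This stands and is the main reason to expect a modest effect. The article also does not say what happens to a randomised patient whose defect fails. A reader might infer that such patients are dropped and that randomisation is thereby lost; no section describes that step.

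Third, a reader might infer from the wording on defects that two defects per patient will enter the t tests as independent values, with an inflated type I error. The documents do not support this. The sample is counted in participants, 12 per arm. The stent and flap descriptions centre on one treated tooth with baseline measurements, although Randomization speaks of a single defect for group A and of several for group B. Baseline stent readings also limit how late a defect could be swapped. What remains is narrower: if allocation precedes the naming of the study defect, that choice could be made with the arm known.

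**Conclusion.** The point holds as a gap in the concealment procedure. The text permits the arm to be known when the last inclusion criterion is judged, does not require the study defect to be fixed before allocation, and contradicts itself on who assigns. The claim that the stated rule limits selection bias therefore goes further than the procedure supports.

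The size is uncertain and probably modest. On the plan's own probing-depth inputs, the loss of two patients per arm would cost about 5 percentage points of power (93.9% to 88.6%). That loss is itself an assumption, since the article gives no failure rate at surgery. Any bias depends on how many patients have more than one eligible defect and how far an operator can judge prognosis, neither of which the documents report. The matter is still worth correcting: the trial is small, and only 4 participants had been enrolled at submission.

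**What to change.** 1. Record one study defect per participant before allocation, for example at the six-week re-evaluation, by a written rule, and use that defect in the analysis.
2. State that the independent clinician releases the assignment only after the study defect has been confirmed at surgery. A patient whose defect fails then never receives an assignment, and 12 per arm needs no change.
3. If that is impractical, either keep every randomised participant in the analysis or have exclusions judged by someone blind to arm. Keeping everyone admits some defects below the depth criterion; blind judgement still loses patients.
4. Reconcile Randomization with Procedure, Overview on who enrols, who holds the list and who assigns.
5. For participants already enrolled, document when the arm was disclosed relative to surgery.

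Items 1 and 4 cost only wording. Item 2 means opening the assignment in theatre with materials for both arms at hand, and A-PRF preparation may add waiting time. The Procedure section describes the blood draw after flap reflection, so later disclosure fits the order of its text, though sentence order is weak evidence of actual timing. The length of any wait cannot be read off the article: Procedure gives 10 minutes of centrifugation for PRF and the Discussion 14 minutes for A-PRF, and these passages must be reconciled.

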### Procedure

#### Overview

Participants will be enrolled and randomly assigned to the interventions by the researchers in charge of the therapy application. Outcome evaluations were performed on the study participants in accordance with the described procedures and outcome measures. The 15-mm University of North Carolina (UNC-15) probe, which measures plaque index, bleeding on probing, probing depth, pocket depth, and clinical attachment loss, will be used to evaluate participants’ periodontal clinical characteristics. Every patient will receive lessons on proper brushing technique as well as a demonstration of good oral hygiene practices.

Following a thorough examination and diagnosis, the first course of treatment will involve root planing under local anesthesia, supragingival and subgingival scaling, and recommendations on oral hygiene. If necessary, a coronoplasty will be carried out. Instructions for plaque control will be repeated until the patient’s plaque score is less than 1. Six weeks after the initial therapy is finished, a re-evaluation will be conducted to assess the patients’ reaction to the treatment and confirm the necessity of periodontal surgery.

A specially made occlusal acrylic stent will be used to standardize the probe’s location and angulations. The occlusal stent will be constructed using acrylic on a cast model created from an alginate impression. The occlusal stent covers the occlusal surface of the tooth being treated as well as the occlusal surfaces of at least 1 tooth that is mesially and distally next to the afflicted tooth. The stent will also be expanded to cover the coronal part of the teeth. A reference point (slot) will be made on the stent at the deepest point of the impacted tooth to allow for repeatable periodontal probe placement. The apical border will be linear and serve as a fixed reference point.

Before the surgery, the patients will be told to rinse their mouths for a minute with a 0.2% chlorhexidine gluconate solution. Because the patient will be draped, only the oral cavity will be visible. Asepsis will be maintained during the procedure. Depending on the operation, either nerve block or infiltration anesthesia will be used for the surgical site using a local anesthetic solution consisting of 2% lignocaine and 1:100,000 epinephrine. The standard technique, which involves a periodontal access flap, will start with intracervical (sulcular) incisions performed on the buccal and lingual parts using Bard-Parker number 12 or 15 surgical blades. The incisions will be made as far interproximally as possible to preserve the entire interdental papillae and accomplish primary wound closure. Two teeth will be included in the flap: one mesial and one distal to the tooth associated with the defect. In the event that more access is required, divergent vertical relief incisions will be made one tooth distant from the problem. The full-thickness (mucoperiosteal) flap will be mirrored using a periosteal elevator (24G; Hu-Friedy) to reveal the alveolar bone in the area of the osseous defect. Extreme caution will be taken to avoid flap rupture or papillae loss when removal of granulomatous tissue from the inner aspect of the flap occurs. To create autologous PRF, the protocol calls for obtaining 6 to 10 mL of venous blood from the patient’s forearm using an 18-gauge needle in a sterile plastic container. The blood will then be transferred to new, sterile test tubes without the addition of any anticoagulant, and the initial volume of blood will be split equally between 2 tubes that are positioned symmetrically around the rotor axis for proper balancing. The tubes will then be centrifuged for 10 minutes at 3000 revolutions per minute (rpm) to create autologous PRF.

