**Objective:**

This study aims to compare and evaluate the effectiveness of AmnioGuard and A-PRF membrane in combination with NovaBone Putty in the regeneration of human periodontal infrabony defects.

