**Methods:**

A total of 24 patients will be selected and divided into 2 groups: group A (n=12, 50%) and group B (n=12, 50%). Group A will receive treatment with NovaBone Putty and AmnioGuard, whereas group B will receive treatment with autologous A-PRF and NovaBone Putty. Plaque index, clinical attachment level, probing pocket depth, complete mouth bleeding score, and intraoral periapical radiographs will be statistically analyzed. Clinical and radiographic features will be evaluated before surgery and 6 months following the procedure.

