## Introduction

### Background

A dysbiotic dental biofilm that gradually destroys bone and periodontal attachment is a hallmark of periodontitis, a chronic, multifactorial, inflammatory illness. This condition negatively affects speech, mastication, aesthetics, psychological well-being, and overall quality of life [1]. On the basis of bone resorption patterns, periodontal defects are traditionally classified as supraosseous (suprabony) or infraosseous (infrabony). Goldman and Cohen [2] further categorized infrabony defects by the number and configuration of residual osseous walls surrounding the periodontal pocket. Infrabony defects pose a significant clinical challenge as they require both structural regeneration and the restoration of periodontal function. Regeneration is defined as “the reproduction or reconstitution of a lost or injured part to restore the architecture and function of the periodontium” [3]. To achieve this, regenerative periodontal therapy aims to stimulate the formation of new bone, periodontal ligament, and cementum. NovaBone Putty, a next-generation calcium phosphosilicate material derived from bioactive glass, offers multiple advantages for regeneration. It is osteoconductive, osteostimulative, and biocompatible, with hemostatic and anti-inflammatory effects. Its premixed formulation enhances clinical handling and allows for optimal defect adaptation [4]. AmnioGuard, a human amniotic membrane (AM)–based barrier, has also gained attention due to its anti-inflammatory, antifibrotic, antibacterial, and antiscarring properties. Its high laminin subunit alpha-5 content supports epithelial adhesion and accelerates healing, whereas its role as a biological barrier aids in preventing epithelial downgrowth—an essential aspect of guided tissue regeneration (GTR) [5-7]. In recent years, biological membranes have become increasingly important in regenerative therapies. Since their initial application in skin grafting in 1910, their role has expanded across medical and dental fields. In particular, AmnioGuard has shown potential to reduce microbial penetration and modulate wound healing responses [8]. In addition, advanced platelet-rich fibrin (A-PRF), rich in leukocytes, contributes to regeneration by releasing growth factors such as transforming growth factor beta 1, epidermal growth factor, and insulin-like growth factor, all of which enhance fibroblast proliferation and tissue healing [9]. Although several studies have assessed the individual regenerative potential of NovaBone Putty and AmnioGuard, limited clinical data directly compare their effectiveness in managing periodontal infrabony defects. A study conducted by Hazari et al [10] compared NovaBone Putty and platelet-rich fibrin (PRF) and concluded that, in comparison to NovaBone Putty alone, PRF in conjunction with NovaBone Putty produced more favorable findings in terms of relative attachment level gain and higher reduction in probing pocket depth (PPD). A study by Kothiwale et al [11] in which they assessed and compared the effectiveness of bovine-derived xenogenic bone graft (Bio-Oss) and demineralized freeze-dried bone allograft using AM as GTR determined that, while there was no discernible difference between the two materials, both showed a notable improvement in bone fill and percentage gain. Furthermore, evidence regarding clinical outcomes such as probing depth reduction, attachment level gain, and bone fill remains sparse [12]. Therefore, this study aims to address this gap by directly comparing the clinical and radiographic outcomes of NovaBone Putty in combination with A-PRF or AmnioGuard in the treatment of infrabony periodontal defects.

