Other characteristics of AmnioGuard, including low immunogenicity, pain relief and epithelialization promotion, self-adhesiveness, and aesthetics, have also been demonstrated. The GTR procedure is frequently carried out in conjunction with the insertion of bone grafts or bone graft replacements beneath the membrane. AM (AmnioGuard) has been used in mouth cavity repair [23]. The interconnected porous structure promotes blood vessel formation, cell occlusiveness, and biodegradability. Proliferation factors included in the AM promote the proliferation of fibroblasts, which speeds up the creation of granulation tissue [24]. Meanwhile, the AM promotes neovascularization in the surrounding tissues and vascularizes good granulation tissue [25]. Additionally, the AM offers a bioactive matrix enhanced with proteins that promotes cell motility. Therefore, it may be hypothesized that using AM as a GTR membrane could encourage cell migration and wound healing as well as vascularization of the granulation tissue in the defects. The tissue of the AM is antibacterial. β-defensins, a significant class of antimicrobial peptides secreted by epithelial cells and a crucial component of the immune system, are produced by amniotic tissue.

A concentrated mixture of growth factors obtained from platelets is known as a platelet concentrate. Four peripheral blood tubes will be taken and put into a centrifuge that has been preprogrammed. Centrifugation will be carried out using the following two procedures: (1) A-PRF with sterile plain glass–based vacuum tubes (10 mL; 1500 revolutions per minute for 14 minutes) and (2) standard PRF with sterile glass-coated plastic tubes (9 mL; 2700 revolutions per minute for 12 minutes).

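### Group B's product is named A-PRF, but the only preparation in the Methods (3000 rpm for 10 minutes) conflicts with the only recipe labelled A-PRF (1500 rpm for 14 minutes)

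*Protocol article*

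**What the plan says.** The comparator is called A-PRF wherever the trial's question or its arms are set out. The Abstract (Objective) is about the "effectiveness of AmnioGuard and A-PRF membrane in combination with NovaBone Putty". The Abstract (Methods) states that "group B will receive treatment with autologous A-PRF and NovaBone Putty". The Introduction (Background) gives the purpose as "directly comparing the clinical and radiographic outcomes of NovaBone Putty in combination with A-PRF or AmnioGuard". The Objectives, Randomization, Procedure for the Control Group and Conclusions sections use the same name.

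The Methods describe one preparation, in Procedure, Overview. It begins "To create autologous PRF, the protocol calls for obtaining 6 to 10 mL of venous blood", divides the blood between two tubes, and ends "The tubes will then be centrifuged for 10 minutes at 3000 revolutions per minute (rpm) to create autologous PRF". The name A-PRF does not appear in this description.

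The Discussion (Expected Findings) gives settings again, worded as a plan: "Centrifugation will be carried out using the following two procedures". The first is labelled A-PRF, at "1500 revolutions per minute for 14 minutes". The second is labelled standard PRF, at "2700 revolutions per minute for 12 minutes".

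**The concern.** An operator who works from the Methods would make group B's membrane at settings that the article does not call A-PRF. An operator who works from the Discussion would use a different speed and a different time. The article itself separates A-PRF from standard PRF and gives each its own settings, so it treats the settings as part of what identifies the product.

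At stake is what the trial can say about its comparator. The objective and the anticipated conclusion concern A-PRF. If the Methods are followed, the finding would apply to a product made at 3000 rpm for 10 minutes, and the article gives no ground for calling that A-PRF. A reader could not tell which product was tested or reproduce it, and two operators could in good faith prepare it differently.

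**Working it through.** No figure in the plan has to be reproduced for this point. The check sets the stated settings side by side.

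| Source | Label in the article | Speed | Time |
|---|---|---|---|
| Methods, Procedure, Overview | autologous PRF | 3000 rpm | 10 min |
| Discussion, Expected Findings, first procedure | A-PRF | 1500 rpm | 14 min |
| Discussion, Expected Findings, second procedure | standard PRF | 2700 rpm | 12 min |

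**Step 1: Methods against the A-PRF recipe.** Speed: 3000 − 1500 = 1500 rpm apart, a ratio of 3000/1500 = 2.0. Time: 14 − 10 = 4 minutes apart, a ratio of 10/14 = 0.71. Both settings differ.

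**Step 2: Methods against the standard PRF recipe.** Speed: 3000 − 2700 = 300 rpm apart. Time: 12 − 10 = 2 minutes apart. Both settings differ here too, so the Methods match neither procedure in the Discussion.

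**Step 3: can one reading reconcile the text?**
- If PRF in the Methods is shorthand for A-PRF, the article gives two incompatible settings for A-PRF.
- If the Methods mean a PRF other than A-PRF, the preparation contradicts the name of the comparator in Randomization and in Procedure for the Control Group.
- If the Discussion text is only background, the Methods are operative, but they do not meet the article's only definition of A-PRF.

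Each reading leaves something to correct.

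**Step 4: who is affected.** All 12 planned group B participants. The Results section reports 4 participants enrolled at manuscript submission, without giving their arm. At least 12 − 4 = 8 of the 12 (8/12 = 67%) were therefore untreated in group B at that date. The bound is reached only if all 4 were in group B and already treated.

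**Step 5: sample size.** The formula in Sample Size Estimations gives (1.96 + 1.64)² × (1.17² + 1.10²) / (8.6 − 6.9)² = 12.96 × 2.5789 / 2.89 = 11.56, rounded up to 12 per group, as stated. No input depends on how the membrane is made, so this point does not change the figure.

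**The case against.** The strongest reply is that the two places do not have equal standing. The Methods give a complete sequence of drawing, dividing and spinning the blood. The Discussion text follows general background on membranes and platelet concentrates, and one of its two procedures belongs to no arm, so it cannot be this trial's operating procedure as written. It may be background put into the future tense. On that view the Methods govern, and what remains is a loose label and a stray paragraph. The word autologous does not separate the products either, because the abstract applies it to A-PRF as well. Without the Discussion, nothing in the article would show that 3000 rpm for 10 minutes is not A-PRF.

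Much of this stands, and it limits how strongly the point can be put. It does not remove it. The Discussion holds the article's only definition of A-PRF, and the Methods do not meet it. Article condensation is no answer, because both recipes are printed and they disagree.

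A second reply concerns the remedy. Recruitment has begun, and moving straight to 1500 rpm could put two preparations into an arm of 12 if anyone has already been treated at 3000 rpm. This stands in full, and the fix below depends on what has been done so far.

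**Conclusion.** The point holds as an internal contradiction about the comparator. The article does not uniquely define what group B receives, and the preparation in its Methods differs in both speed and time (by 1500 rpm and 4 minutes) from the only recipe it labels A-PRF. It should be fixed. The conclusion rests on the printed settings and labels alone. It does not assume which preparation is used in practice, which the article leaves open.

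A reader might infer more than the document supports:
- **That group B actually receives standard PRF.** The Methods settings lie numerically nearer to that recipe, but they do not match it. Without a rotor radius, nearness in rpm says little about the product.
- **That the centrifugal force is four times too high.** The ratio (3000/1500)² = 4.0 assumes equal rotor radii, which the article does not give.
- **That blood volume and tube number also conflict.** The Discussion mentions four tubes without saying how many are for A-PRF, or whether 10 mL is a fill volume.
- **That the trial is invalid or underpowered.** The randomised comparison is valid for whatever product is used consistently, and no effect on bone fill, probing depth or attachment level has been shown.

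The bound of 8 untreated participants applies only at manuscript submission. Current enrolment is unknown.

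**What to change.** First establish which preparation was used for any group B participant already treated. Then:

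- **If none has been treated:** state the A-PRF settings of the Discussion, 1500 rpm for 14 minutes, as the single preparation in Methods, Procedure, Overview, in place of 3000 rpm for 10 minutes.
- **If some were treated at 3000 rpm for 10 minutes:** keep those settings for the whole arm. Rename the comparator to the PRF actually used in the objectives (abstract and main text), Randomization and Procedure for the Control Group, with the other mentions of the arm to match. Limit the Conclusions section to that product.

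In either case, remove the conflicting recipe and the unused standard PRF procedure from Expected Findings. Record and report the preparation used for each group B participant. The single description should give blood volume, tube type and number, speed with rotor radius or g-force, and time.

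The cost is text edits (two sections in the first case; in the second, the sections that name the arm plus Expected Findings) and one recorded field per group B participant. No extra patients are needed. An ethics committee notification may be required if the preparation adopted differs from the approved full protocol, which is not shown.
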